#### Motivational interviewing

Motivational interviewing (MI) is a patient-centered counseling technique that describes readiness to change as a dynamic rather than a static state [14]. MI is aimed at eliciting behavioral change by exploring and resolving a patient’s ambivalence. MI has been successfully used to increase adherence to long-term treatment and promote behavioral change in other medical fields [15–17].

Several studies have investigated the impact of MI on HA use [6, 18, 19]. However, these studies have had significant limitations. Aazh et al. [6] and Ferguson et al. [19] studies were only pilot studies and had limited power, while Solheim et al. [18] did not use a control group. Furthermore, none of the above studies considered the long-term outcomes of MI and whether these positive results would persist. A recent systematic review found no robust evidence that MI significantly improved HA use or user-reported outcomes, and concluded that future research is warranted [20].

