### Objectives {7}

The primary objective is to determine the efficacy of one-on-one MI in increasing adherence to HA use in new adult clients in the short and long terms. The secondary objective is to determine if there are adverse effects associated with one-on-one MI.

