### Hypothesis

Standard audiological care with one-on-one MI does not alter HA use compared to standard audiological care alone in new adult HA clients.

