### Outcomes {12}

#### Primary outcomes

The primary outcome is the inter-group difference in average hours of HA use at 1, 3, 6, and 12 months post-intervention aimed at assessing the early and long-term effect of the intervention. This is a quantitative measure recorded by the HAs data-logging feature.

The secondary outcomes are differences in inter-group average participant-completed questionnaire (IOI-HA) [21] scores at 1, 3, 6, and 12 months post-intervention and reported complications. The IOI-HA is an established rigorous patient reported measure for HA effectiveness [22, 23].

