### Sample size {14}

Aazh et al.’s [6] feasibility investigation of assessing HA data-logged hours of use in response to MI concluded that a standardized difference of 0.6 was best for sample size estimation. Therefore to discern this difference or greater at a 5% significance level with a power of 80%, 45 patients will be required in each intervention arm based on Machin and Campbell’s [21] clinical trial design tables. Therefore, 90 participants in total at a randomization ratio of 1:1.

An allowance of 50% participant dropout rate was adopted in this study as opposed to the 20% drop out identified by Aazh et al. to compensate for the uncertainties or anticipated higher drop rate due to the COVID-19 pandemic [6]. This higher rate is reasonable because a previous hearing aid RCT trial conducted by our senior investigators who recruited participants from audiology clinics within the greater Vancouver area, in part over the pandemic period with 3 months’ follow-up, resulted in 39.1% of participant data in the intervention arm being unavailable because of participants’ failure to attend follow-up or complete study questionnaires fully [24]. This leads to an adjusted sample size of 180 participants, 90 per group.

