## Statistical methods

### Statistical methods for primary and secondary outcomes {20a}

Descriptive Statistics will be used to summarize patient demographics. Independent samples *T*-tests will be used to compare continuous variables such as PTA averages, word recognition scores, and data-logged hearing hours between groups. Chi-squared test will be used to determine the degree of association between categorical variables such as patient-reported outcome, sex, and age group. A univariate linear regression will be run with demographic variables and data-logged hearing hours. Pearson’s correlations will also be used to measure the strength of associations between data-logged hearing aid use hours and self-reported measures via the IOI-HA questionnaire. Data will be analyzed using SPSS (Version 25).

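### The planned t-tests can test the MI effect at each visit, including 12 months, but nothing in the plan estimates how that effect changes between visits

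*Protocol article*

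**What the plan says.** The background (Motivational interviewing) criticises earlier studies because "none of the above studies considered the long-term outcomes of MI and whether these positive results would persist". The primary objective (Objectives {7}) is to "determine the efficacy of one-on-one MI in increasing adherence to HA use in new adult clients in the short and long terms". Under Primary outcomes, the between-arm difference in average hours is taken at four time points and is "aimed at assessing the early and long-term effect of the intervention". No visit is singled out as primary.

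The section Statistical methods for primary and secondary outcomes {20a} gives one between-arm method for hours: independent-samples t-tests, which "will be used to compare continuous variables such as PTA averages, word recognition scores, and data-logged hearing hours between groups". Its only regression is univariate and relates hours to demographic variables. No repeated-measures model, arm-by-visit term or change-in-effect contrast is stated.

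Three other provisions matter here:
- Plans for assessment and collection of outcomes {18a} labels the 1-month assessment as pre-intervention, with MI delivered after it. The visits that can show an MI effect are therefore 3, 6 and 12 months.
- Intervention description {11a} has each reading average daily use since the previous one. The 12-month value thus covers roughly months 6 to 12.
- The retention section {18b} keeps data gathered before withdrawal for analysis, whereas {20c} drops participants whose hours or IOI-HA scores are missing or incomplete.

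**The concern.** Separate t-tests give one result per visit. None of them compares the arm difference at 12 months with the arm difference at 3 months, so none measures waning or maintenance. Yet the repeated visits over a year are what distinguish this trial from its predecessors.

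With nothing else planned, a reader of the results could judge persistence only by eye, most likely from which visits reached p < 0.05. That pattern is unreliable. Two estimates of the same underlying effect can fall on opposite sides of the threshold by chance, and a significant result followed by a non-significant one is not evidence of change. The readings come from the same participants, so the change can be estimated directly from data the trial already collects.

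**Working it through.** **Inputs from the protocol (Sample size {14}).** The size was set "at a 5% significance level with a power of 80%, 45 patients will be required in each intervention arm", on the basis that "a standardized difference of 0.6 was best for sample size estimation". The standardized difference is not tied to a visit. Sidedness is not stated. I take it as two-sided because the hypothesis is worded as no alteration of use.

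**Reproducing the plan's figure.** Two-sample t-test, d = 0.6, two-sided 5%, power 80%: the noncentral t gives 44.6, so 45 per arm, with power 0.804 at 45. A one-sided test gives 35 (normal approximation), which does not match. With 50% dropout, 45 / 0.5 = 90 per arm and 180 in total. The stated figures reproduce.

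**Assumptions not in the documents.** Equal SD at each visit, normal test statistics, no covariate adjustment, 45 analysed per arm at both visits, and between-visit correlation ρ of 0.5 to 0.8.

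**What the 12-month test can do.** Power is 80% if the true 12-month difference is 0.6 SD and 29% if it is 0.3 SD.

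**How often a constant effect looks like fading.**
- Standard error of one visit's difference: √(2/45) = 0.211 SD.
- Expected test statistic at each visit: 0.6 / 0.211 = 2.85.
- Chance that one visit is not significant (normal approximation): Φ(1.96 − 2.85) = 0.188.
- Chance of significant at 3 months but not at 12: 0.188 minus the bivariate normal probability that both are non-significant.

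| ρ | Both non-significant | Significant at 3, not at 12 | Tests disagree in either direction |
|---|---|---|---|
| 0.5 | 0.080 | 0.108 | 0.216 |
| 0.7 | 0.104 | 0.084 | 0.167 |
| 0.8 | 0.120 | 0.068 | 0.136 |

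Across 3, 6 and 12 months together, with the same constant effect, a mixed pattern of significance occurs in 33%, 25% and 21% of trials at these three correlations.

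**What the direct contrast gives.** For the 12-minus-3-month change in the arm difference, SE = √(2(1 − ρ)) × √(2/45).

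| ρ | SE (SD units) | 95% half-width = 1.96 × SE | Power, 0.6 to 0.3 SD | Power, 0.6 to 0 |
|---|---|---|---|---|
| 0.5 | 0.211 | 0.41 | 0.30 | 0.81 |
| 0.7 | 0.163 | 0.32 | 0.45 | 0.96 |
| 0.8 | 0.133 | 0.26 | 0.61 | 0.99 |

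For comparison, the half-width for a single visit's difference is 1.96 × 0.211 = 0.41 SD. When nothing changes, the contrast errs in 5% of trials over both directions, so 2.5% in the direction of fading.

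The half-widths also show the contrast's limit. An estimated change of exactly zero would still be compatible with a loss of 0.3 SD at ρ = 0.5 or 0.7 (0.41 and 0.32 both exceed 0.3), but not at ρ = 0.8 (0.26).

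**The case against.** The strongest defence is that the objective and the primary outcome can be read as asking only for an early effect and a late effect. Visit-specific comparisons answer both, and the 12-month comparison is randomised and adequately powered at 0.6 SD. This stands, subject to the exclusions in {20c}. A reader might infer that t-tests cannot show whether an MI effect lasts. The protocol does not support that: a clear 12-month difference with its interval does show a lasting effect.

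A reader might also infer that the investigators intend to compare p-values between visits. No section says so. Even the visit-by-visit use of the t-test is a reading of the outcome and methods sections together, though the natural one.

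Two further inferences fail. Unequal numbers at 3 and 12 months would add to the discordance, but {20c} most naturally puts the same complete cases into every visit. And significance at both visits after a true halving is not a false claim, because 0.3 SD at 12 months is still an effect.

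Finally, it can be said that a change-in-effect contrast is detail for an analysis plan that is not shown. That has some weight, but {20a} does name its method, and the named method does not address persistence, which the background gives as a reason for the trial.

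**Conclusion.** The point holds in a limited form. The stated t-tests are valid for the effect at each post-intervention visit but supply no estimate or test of how it changes. Reading persistence from the pattern of significance would mislead in about 7% to 11% of trials when the true effect is a constant 0.6 SD. That range rests on 45 analysed per arm, equal SDs and an assumed correlation of 0.8 to 0.5, and the harm arises only if results are read that way.

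The direct contrast is the better tool, but it is not decisive alone. Its power for a halving is about 30% to 60%, and a value near zero is equally expected if MI never worked. This is a worthwhile, inexpensive improvement. It is not a flaw that invalidates the primary comparison or the sample size.

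**What to change.** In {20a}, replace the separate t-tests on post-intervention hours with one repeated-measures mixed model:
- **Outcome:** hours at 3, 6 and 12 months, with readings correlated within participant.
- **Terms:** arm, visit and arm-by-visit, adjusted for the pre-intervention 1-month reading.
- **Data:** all available post-intervention readings, as {18b} implies. Amend the exclusion in {20c} to match. This relies on readings being missing at random given those observed, which should be stated.
- **Reporting:** the arm difference at each visit with its 95% confidence interval, and the 12-minus-3-month change in that difference as an estimate with its 95% confidence interval.
- **Interpretation:** base any statement on persistence on the 12-month difference together with that change. Do not base it on which visits are significant, or on a non-significant contrast alone.

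The cost is a change of wording and slightly more analysis work, using a standard mixed-model procedure in the software already named. It needs no new data, visits or participants, and the sample size stands for the visit-specific test. Low power for partial waning remains and should be acknowledged in the report.

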**Methods:**

A multi-center, prospective, randomized patient-blind controlled trial with a pre- and post-tests design. New hearing aid users ≥ 18 years of age will be recruited from Vancouver, Canada. They will be randomly assigned to a treatment or control group. The treatment group will attend a one-on-one MI session hosted by a practicing MI therapist in addition to standard in-person audiological care. The control group will receive standard in-person audiological care. Data is collected at baseline and at 1, 3, 6, and 12 months’ follow-ups. The primary outcomes are data-logged hearing aid use hours and patient-reported outcomes as measured by the International Outcome Inventory for Hearing Aids questionnaire. Associations between intervention and hearing aid use hours and self-reported outcome measures will be assessed.

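### The IOI-HA outcome is defined as a difference in average scores, but the analysis section classes it as categorical for a chi-squared test and names no comparison of mean scores

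*Protocol article*

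**What the plan says.** Under Outcomes {12}, the protocol article states: "The secondary outcomes are differences in inter-group average participant-completed questionnaire (IOI-HA) [21] scores", at 1, 3, 6 and 12 months. The target is therefore a difference between two means.

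The paragraph on statistical methods for primary and secondary outcomes {20a} then does three things:

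- It assigns independent-samples t-tests to "compare continuous variables such as PTA averages, word recognition scores, and data-logged hearing hours between groups". The IOI-HA is not among the examples.
- It assigns the patient-reported outcome to a different test: "Chi-squared test will be used to determine the degree of association between categorical variables such as patient-reported outcome, sex, and age group".
- It plans Pearson correlations for the "strength of associations between data-logged hearing aid use hours and self-reported measures via the IOI-HA questionnaire", which requires a numeric score.

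The term patient-reported outcome can only mean the IOI-HA. The abstract speaks of "patient-reported outcomes as measured by the International Outcome Inventory for Hearing Aids questionnaire", and no other questionnaire is planned. The abstract and Table 2 list it as primary, while Outcomes {12} calls it secondary.

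**The concern.** Within one paragraph the same variable is categorical for one method and numeric for another, and the categorical label conflicts with the outcome definition. Pearson's chi-squared test asks whether the distribution over categories differs between arms. It returns no mean difference, no confidence interval and no direction, and its result does not change if the categories are reordered. An analyst who followed {20a} literally would not produce the quantity promised in {12}. That analyst would also have to choose cut-points that the article does not give, and would use a test with less power against a shift in scores. The IOI-HA is a main endpoint whichever of the two labels applies, so this matters for what the trial can report.

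**Working it through.** **Inputs.** Sample size {14} gives a 5% significance level, 80% power, 45 per arm, 1:1 allocation and a 50% dropout allowance. Its effect size is for data-logged hours: "standardized difference of 0.6 was best for sample size estimation". Sidedness is not stated, so two-sided is assumed. No effect size, SD or category scheme is given for the IOI-HA. Borrowing 0.6 SD for it is an assumption, and 0.4 and 0.5 SD are shown as a range.

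**Step 1: reproduce the plan's figure.** The normal approximation is n = 2(1.960 + 0.842)² / 0.6² = 43.6, so 44 per arm. The t-test calculation gives 44.6, so 45 per arm. Then 90 / (1 − 0.5) = 180. The stated 45 per arm and 180 in total both reproduce.

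**Step 2: t-test on the score.** The noncentrality is d√(n/2) = 0.6 × √22.5 = 2.846 on 88 degrees of freedom, which gives 80.4% power.

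**Step 3: chi-squared on the same score.** Take normal scores with equal spread whose means differ by d SD. Cut them at pooled quantiles into k equally likely categories. With category probabilities p₀ⱼ and p₁ⱼ and their average p̄ⱼ = 1/k, the noncentrality is

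λ = n Σⱼ [(p₀ⱼ − p̄ⱼ)² + (p₁ⱼ − p̄ⱼ)²] / p̄ⱼ,

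and power is the chance that a noncentral chi-squared variable on k − 1 degrees of freedom exceeds its 5% critical value.

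- k = 2, d = 0.6: the two arms have probabilities 0.618 and 0.382 of falling below the cut. λ = 45 × 4 × 0.118² / 0.5 = 5.0 against a critical value of 3.84, so power is 61%.
- k = 5, d = 0.6: the probabilities are 0.281, 0.233, 0.200, 0.167, 0.119 in one arm and the reverse in the other. λ = 6.88 against a critical value of 9.49, so power is 53%.

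| Power at 45 per arm | t-test on score | χ², 2 categories | χ², 3 | χ², 5 | χ², 8 |
|---|---|---|---|---|---|
| d = 0.6 | 80% | 61% | 60% | 53% | 45% |
| d = 0.5 | 65% | 47% | 45% | 39% | 32% |
| d = 0.4 | 47% | 32% | 30% | 26% | 21% |

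Simulation with 20,000 runs at d = 0.6 gave 60%, 61% and 54% for 2, 3 and 5 categories, in line with the formula.

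**Step 4: where the loss comes from.** The full score carries a squared noncentrality of 2.846² = 8.10 on one degree of freedom. Two categories keep only 5.0 of it. Five categories keep 6.88 but spread it over four degrees of freedom. On those same five categories, a t-test on the category numbers keeps about 76% power (simulation) against 53% for chi-squared. With five categories, most of the loss therefore comes from ignoring the order.

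**Step 5: the same loss in participants.** For 80% power at d = 0.6, chi-squared needs about 71 per arm with 2 or 3 categories and 79 per arm with 5, against 45 for the t-test.

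**The case against.** The strongest reply is that the text does not make chi-squared the only analysis. The t-test list opens with such as, so mean IOI-HA scores could fall under it. The chi-squared sentence does not name the IOI-HA or say that it compares arms. The article also condenses a fuller plan. On that reading, a t-test on mean scores and a chi-squared test on grouped responses would sit side by side. Part of this stands: an intended t-test cannot be ruled out. But the article does not leave the variable's type open. It calls the patient-reported outcome categorical, and that conflicts both with {12} and with the Pearson correlation. If single items were meant, they would be ordered responses and the order would still be ignored.

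A second reply is that 45 per arm is what remains after the full 50% dropout, since 90 per arm are to be randomised. This is fair. With all 90 analysed and d = 0.6, the same formulas give 98% for the t-test against 89%, 89%, 86% and 80% for 2, 3, 5 and 8 categories. The loss is smaller there, but it remains.

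Three stronger readings are tempting, and the documents do not support them:

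- A reader might infer that a real IOI-HA benefit is likely to be missed. The effect size is borrowed from hours of use, and even so chi-squared power exceeds one half with 2 to 5 categories at d = 0.6.
- A reader might infer that chi-squared would give false positives when only the spread of scores differs. The documents give no spread and no cut-points, so no figure can be attached. A rejection there would also be no error for a test whose null hypothesis is equal distributions.
- A reader might infer that the sample size is wrong. It rests on hours of use and it reproduces.

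**Conclusion.** The point holds as an inconsistency between the outcome definition and the named test. As written, {20a} gives the IOI-HA a test that cannot estimate the difference in averages defined in {12}, names no comparison that can, and types the score in two incompatible ways. This part rests on the wording alone.

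The loss of power is illustrative. At 45 per arm with 2 to 5 equally likely categories it is about 14 to 27 percentage points over d = 0.4 to 0.6, and more with finer categories. It assumes normal scores with equal spread, a two-sided 5% test and an effect size that the documents do not give for the IOI-HA. The correction should be made. It affects the questionnaire comparison only and leaves the sample size of 180 as it is.

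**What to change.** In {20a}, delete the patient-reported outcome from the chi-squared sentence. Add that mean IOI-HA scores are compared between arms as a quantitative outcome at each follow-up, by t-test or linear model, reporting the mean difference with a 95% confidence interval. If single items are also to be compared, name a method that uses their order. The cost is one sentence, with no change to data collection or sample size.

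Adjusting the 3-, 6- and 12-month comparisons for the 1-month score, which {18a} places before the intervention, is an optional refinement. It would be a new model, because the article plans t-tests for hours and contains no adjusted between-group model to borrow. It would also use as a covariate a time point that {12} lists as an outcome, so that listing would need to be settled first.

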### Interim analyses {21b}

Initial interim analysis will be performed when 30% of the participant recruitment is achieved to determine that the intake characteristics (age, sex, and degree of hearing loss) are similar in both arms. A second interim analysis will be performed when 50% of the recruited participants’ follow-up data is available to determine if a difference is evident in the outcomes. The results will guide the decision to continue the study.

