## Assignment of interventions: allocation

### Sequence generation {16a}

Participants will be allocated to the study group by block randomization. The block sequence will be generated using the computer-generated STATA statistical package (Version 16). Block size variation will be used to prevent the prediction of treatment. Allocationwill be performed by the study coordinator who will not be involved in data collection; patients will be assigned a non-identifiable number sequence.

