### Frequency and plans for auditing trial conduct {23}

Study-related monitoring, audits, and inspections by the clinical research ethics board of all study-related documents will be performed when 30% of participant recruitment is achieved. The PI will also ensure the legitimacy and capability for inspections of facilities. A second audit will be performed when 50% of the recruited participants’ follow-up data is available. The results will guide the decision to continue the study.

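### Baseline similarity between randomised arms at the 30% look should not inform continuation; drop the baseline tests and adjust the hours comparison for baseline covariates instead

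*Protocol article*

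**What the plan says.** All of this is in the protocol article.

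- **Interim analyses {21b}.** The timing is given as "Initial interim analysis will be performed when 30% of the participant recruitment is achieved", and the purpose is "to determine that the intake characteristics (age, sex, and degree of hearing loss) are similar in both arms". A later look, this one at outcomes, is then described: "A second interim analysis will be performed when 50% of the recruited participants’ follow-up data is available to determine if a difference is evident in" (quotation cut before its last words). The section closes: "The results will guide the decision to continue the study". It gives no definition of similarity, no test, no threshold, and no action if the arms differ.
- **Sequence generation {16a} and Concealment mechanism {16b}.** "Participants will be allocated to the study group by block randomization". Blocks are computer-generated and vary in size. Envelopes are opaque, sealed and sequentially numbered, and recruiting audiologists cannot see the sequence. No stratification by age, sex or hearing loss is described.
- **Statistical methods {20a}.** Independent-samples t-tests "will be used to compare continuous variables such as PTA averages, word recognition scores, and data-logged hearing hours between groups". PTA and word recognition appear in Table 2 as baseline assessments only, so for these two variables this is baseline significance testing. Hours of use, the primary outcome in Outcomes {12}, gets the same unadjusted test. A univariate regression of hours on demographic variables is also planned, but it is not described as adjusting the comparison of arms.

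**The concern.** The 30% look asks whether randomisation produced similar arms. Where allocation was random and concealed, a test of that kind addresses a null hypothesis already known to be true. A significant difference does not show bias. A non-significant one does not show that the arms are alike, least of all with about 27 per arm. Neither result bears on whether the trial should go on.

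Two things are at stake. First, if the closing sentence of {21b} covers the first look, a sound trial could be called into question because of chance imbalance. The protocol dispenses with a data monitoring committee, so no independent body is named to put such a finding in perspective. Second, the plan looks for imbalance but states no remedy for it. The unadjusted t-test is valid on average over randomisations. In the trial actually run, though, an imbalance in a covariate that predicts hours shifts the estimated difference, by roughly the imbalance times the covariate's slope on hours. The planned test leaves that shift in place.

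**Working it through.** **Inputs from the protocol (Sample size {14}, Interim analyses {21b}).** Standardised difference 0.6, 5% significance, 80% power, 45 per arm, 1:1 allocation, 50% dropout allowance, 180 in total; first look at 30% of recruitment; three characteristics compared.

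**The plan's own figure.** The normal approximation, two-sided, gives n = 2 × ((1.960 + 0.842)/0.6)² = 43.6, so 44 per arm. The t-test calculation gives 44.6, so 45, with 80.4% power at 45. A one-sided test would give 35 and does not fit. Then 2 × 45 = 90, and 90/(1 − 0.5) = 180. The stated sample size reproduces.

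**Size of the first look.** 0.30 × 180 = 54 participants, about 27 per arm.

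**How often perfect randomisation would look dissimilar.** The protocol gives no criterion, so every cut-off below is an assumption.

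- Three independent tests at 5%: 1 − 0.95³ = 1 − 0.857 = 0.143.
- Three independent tests at 10%: 1 − 0.90³ = 1 − 0.729 = 0.271.
- Simulation at 27 per arm (two t-tests and one chi-squared test at 5%, 40,000 replicates, equal sex split assumed): 13.8%, 13.4% and 13.0% when the correlation of age with hearing loss is 0, 0.3 and 0.5. Correlation changes little.
- Cut-offs on the standardised difference, treating all three characteristics as independent and approximately normal: the standard error is √(2/27) = 0.272.

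| Assumed cut-off | One characteristic exceeds it | At least one of three |
|---|---|---|
| 0.20 | 0.462 | 0.845 |
| 0.25 | 0.358 | 0.736 |
| 0.50 | 0.066 | 0.186 |

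Across these assumptions the chance of a flag runs from about 13% to about 84%, with nothing wrong in the allocation.

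**What a reassuring result would mean.** By the normal approximation, a 5% test stays non-significant up to a standardised difference of about 1.96 × 0.272 = 0.53. An imbalance close to the trial's target effect of 0.6 could therefore pass as similar.

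**Effect of the change.** If between-arm similarity has no bearing on continuation, the chance that random baseline imbalance triggers that decision is zero. The sample size stays at 180.

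**The case against.** The strongest reply is that {21b} may not say what it is feared to say. Its closing sentence directly follows the second look, which concerns outcomes and is the natural trigger for a continuation decision. That reading is open. So is the wider one, because the sentence comes after both looks are described and speaks of results without distinguishing them. The text has to settle this. Even on the narrower reading, the 30% comparison has no sound stated use.

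A reader might look for support in Frequency and plans for auditing trial conduct {23}, which uses the same 30% and 50% points and the same closing sentence. It gives none: its results are those of ethics-board audits, not of baseline comparisons.

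It is also true that no test is prescribed at the 30% look. {20a} does not mention interim analyses, lists PTA but not age among its t-tests, and opens with descriptive summaries of demographics. The 14% is therefore not a property of the plan.

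A baseline look can expose faulty or subverted allocation, and with one coordinator handling envelopes in a multi-centre trial that is worth checking. But the stated purpose is similarity, and conduct is better checked directly against the sequence and the envelopes.

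A reader might further infer that allocation would be altered midway. Nothing in the protocol suggests it, and {25} requires a formal amendment and ethics approval for design changes.

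Finally, covariates may be set out in an analysis plan not shown. The protocol nevertheless states a t-test for hours, and that stated choice is what is questioned here.

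**Conclusion.** The point holds in a limited form. A between-arm similarity check at 54 of 180 participants cannot usefully inform continuation under concealed randomisation, and the wording of {21b} allows it to. The baseline t-tests in {20a} have the same weakness, and the unadjusted t-test on hours leaves chance imbalance where it falls.

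The 14% and 27% figures are illustrations that rest on three independent tests at assumed levels. The document fixes neither a test nor a level. It would be too strong to say that the plan contains a stopping rule for baseline imbalance: it has no rule, only a sentence of uncertain reach.

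The weight is moderate. A look at baseline data alone spends no type I error on the outcome, and the outcome look at 50% in the same section is the more serious matter. This point is still worth correcting, because a better method is available at almost no cost.

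**What to change.** 1. In Interim analyses {21b}, state that the 30% look does not feed the continuation decision. Limit it to pooled recruitment, data quality and randomisation conduct (sequence and envelope checks), and say which look the closing sentence refers to.
2. In Statistical methods {20a}, remove the significance tests on baseline variables and report baseline by arm descriptively.
3. Replace the unadjusted t-test on hours with a linear model (ANCOVA) that includes allocation and prespecifies age, sex and PTA, whatever balance is observed.
4. Add 1-month hours as a covariate only once the protocol is reconciled on what that value is. Outcomes {12} counts 1 month among the post-intervention primary timepoints, whereas the 1-month heading under {18a} calls it pre-intervention.

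The cost is small. One comparison loses its decision role, and the covariates are already collected. The rules in {20c} for missing age and sex need a matching line, because the current wording leaves missing sex out of analysis and an adjusted model must say how such participants are handled.
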